**Methods:**

This is a multicenter, three-arm, randomized controlled clinical trial. The study will include patients older than 3 years of age with epilepsy who have had medically refractory seizures for at least 2 years and are eligible for surgical treatment with an epileptogenic focus as determined by multidisciplinary evaluation prior to randomization. The primary outcome measure is seizure outcome (quantified by seizure remission rate) at 3-month, 6-month, and 1-year follow-up after treatment. Postoperative neurologic impairment, spectrum distribution change of video electroencephalogram, quality of life, and medical costs will also be assessed as secondary outcomes.

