## Methods/design

### General study design

A multicenter, randomized controlled, parallel-group clinical trial will be conducted at Sanbo Brain Hospital, Beijing Tiantan Hospital, and Xuanwu Hospital. This study has been registered in the Chinese Clinical Trial Registry before the enrollment of participants (http://www.chictr.org.cn, registration number: ChiCTR2200060974).

Participant baseline information will be collected approximately 10 days before surgery, including participant demographics, seizure status, use of ASMs, neurological status, electroencephalogram (EEG), and magnetic resonance imaging (MRI) findings. The perioperative information of the participants will be recorded based on the surgical records and anesthesia records, including length of operation, amount of bleeding, complications, and cost of operation. The participants will be followed up for three times at 3, 6, and 12 months after the operation. The timeline of this study is shown in Fig. 1. The baseline information mainly includes the following:Seizure condition: seizure frequency (time/month), seizure duration, severity, etc.Neurological impairment: neurological function physical examination and National Institutes of Health Stroke Scale (NIHSS) score.Use of anti-seizure medications: type and dosage of drugs.Preoperative EEG examination: scalp EEG spectrum distribution, EEG Epileptogenic Index, etc.Preoperative MRI.Quality of life: using the Quality of Life in Epilepsy-89 scale for adults (ages 17–60) and the Quality of Life in Epilepsy-48 scale for children (ages 14–16). Patients not in the above age range will not be assessed for quality of life.Cognitive function: using the Chinese version of the Wechsler Intelligence Scale-IV and the Chinese version of the Wechsler Development Scale-IV.

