#### Secondary outcomes

Engel classification at one-year follow-up after surgery.The proportion of participants with neurologic impairment after surgery, primarily determined by the change in NI.SHH scale score at each post-operative visit and neurological physical examination findings at each post-operative visit.Spectrum distribution and Epileptogenic Index change of video EEG at each post-operative visit.Participants’ quality of life after treatment. Evaluation will be performed at each post-operative visit by the Quality of Life in Epilepsy-89 scale (adults > 17 years) and the Quality of Life in Epilepsy-31 scale (children 4–16 years).Epilepsy-related medical costs at each post-operative visit.

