### Statistical analysis

Statistical analysis will be mainly performed by researchers from Sanbo Brain Hospital, Capital Medical University, using the SAS 9.3 (SAS Institute Inc., Cary, NC, USA) software. Take the test level *α* = 0.05. The Kolmogorov-Smirnov test will be used to test whether the variables will be normally distributed. Measurement data conforming to normal distribution will express as mean ± standard deviation (‾X ± s), and measurement data not conforming to normal distribution will be expressed as interquartile range *M* (Q25, Q75). The *t*-test will be used to compare the normal distribution of continuous variables. The rank sum test will be used to compare the continuous variables that do not conform to the normal distribution. The chi-square test will be used to compare the categorical data. Univariate and multivariate methods will be used to analyze the preoperative and operative factors associated with seizure-free. Analysis of the primary outcome will be by intention-to-treat.

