**Outcomes**							
Seizure remission rate					X	X	X
Engel classification							X
ASMs		X		X	X	X	X
Neurological function examination		X		X	X	X	X
Scalp EEG		X			X	*X	X
NISHH		X					X
WAIS-IV-C/WCIS-IV-C		X					X
WADS-IV-C/WCDS-IV-C		X					X
QOILE-89/QOILE-48		X					X
PET		*X					*X
MRI		X			X	*X	X
Operative information			X				X
Adverse events				X	X	X	X

*X*, required; **X*, optional; *LITT* Laser interstitial thermal therapy, *EEG* Electroencephalography, *RF-TC* Radiofrequency thermocoagulation, *ASM* Anti-seizure medications, *WAIS-IV-C* Chinese version of the Wechsler Adult Intelligence Scale-IV, *WCIS-IV-C* Chinese version of the Wechsler Children’s Intelligence Scale-IV, *WAIS-IV-C* Chinese version of the Wechsler Adult Development Scale-IV, *WCIS-IV-C* Chinese version of the Wechsler Children’s Development Scale-IV, *QOLIE-89* Quality of Life in Epilepsy-89, *QOLIE-48* Quality of Life in Epilepsy-48, *PET* positron emission tomography, *MRI* Magnetic resonance imaging

All related data will be collected and entered into an eCRF and study database. The investigators and clinical coordinators will be responsible for ensuring that the required data are collected and entered into the eCRF. The original information will be kept in paper medical records for data traceability purposes. The eCRF will be printed as a paper version and stored in a dedicated locked filing cabinet.

Only authorized researchers will be allowed to process the research data under computer password protection. The final data will be anonymized by completely removing any participant’s identifying information.

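### Skewed medical costs would be compared by a rank sum test and medians, which do not estimate the difference in mean cost and can disagree with it in either direction; the cost outcome also does not say whether the operation is counted (minor)

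*Protocol article*

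**What the plan says.** The abstract of the protocol article says that "quality of life, and medical costs will also be assessed as secondary outcomes", and the Secondary outcomes section lists "Epilepsy-related medical costs at each post-operative visit".

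The Statistical analysis section gives one chain for continuous variables, at a test level of 0.05. First, "The Kolmogorov-Smirnov test will be used to test whether the variables will be normally distributed". Variables that pass are summarised by mean and standard deviation and compared by t-test. For the rest, "measurement data not conforming to normal distribution will be expressed as interquartile range" (the symbols that follow show median and quartiles), and "The rank sum test will be used to compare the continuous variables that do not conform to the normal distribution". Costs are not named or exempted.

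The cost of the operation appears in General study design, among the perioperative items to be recorded: "including length of operation, amount of bleeding, complications, and cost of operation". Table 1 has no row for costs. Its row "Operative information" is marked at the operation and again at 365 days.

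**The concern.** Costs are usually right-skewed, so the normality test will tend to send them to ranks and medians. What a hospital or payer spends is the mean cost per patient times the number of patients. A rank test gives one very expensive patient hardly more weight than a slightly expensive one, and a median ignores the size of the upper tail. If the two arms have differently shaped cost distributions, the reported result can show a cost difference where the means are equal, or point the opposite way from the means.

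Unequal shapes are plausible here. The lesioning arm is a 4:1 mixture of two technologies set against one resection arm. The abstract expects fewer seizure-free patients after lesioning, and the Sample size section expects more neurological impairment after resection (11% against 2%). These features could lengthen the tail of either arm.

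A second, smaller matter is what counts as cost. The operations are what the trial compares, yet the outcome is worded by post-operative visit and does not say whether the operation itself is included.

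**Working it through.** **Figure to reproduce.** The article states no cost figure, so none can be reproduced. The sample size of 240 is used only to set the group size.

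**Inputs from the article.** 240 patients randomised 1:1 gives 120 per arm. With 20% withdrawal, 120 × (1 − 0.20) = 96 per arm. The test level is 0.05. Its sidedness is not stated for this comparison, so two-sided is used here.

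**Inputs assumed.** All cost distributions are assumptions.

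**Step 1: does the normality test send costs to ranks?** Simulated log-normal samples of 96 were tested by Kolmogorov-Smirnov in two forms: with fitted mean and SD and standard tables, and with the Lilliefors correction. Normality was rejected in 41% and 94% of samples at log-scale SD 0.5, in 83% and 99.6% at 0.7, and in 99.6% and 100% at 1.0. Skewed costs usually go to ranks. Mildly skewed costs may not, depending on how the test is run.

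**Step 2: why ranks and means separate.** A log-normal cost with log-scale mean μ and SD s has median exp(μ) and mean exp(μ + s²/2). With equal means, the median ratio (lesioning to resection) is exp(−(s_L² − s_R²)/2). For s_L = 1.0 and s_R = 0.5 this is exp(−0.375) = 0.69. The chance that a lesioning patient costs less than a resection patient is Φ(0.375/√(1.00 + 0.25)) = Φ(0.335) = 0.63. The rank test responds to this 0.63, although the mean difference is zero.

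**Step 3: size at 96 per arm, two-sided 0.05, equal true means.**

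| Log-SD lesioning / resection | Median ratio | Rank sum result |
|---|---|---|
| 0.7 / 0.7 | 1.00 | cheaper in 2.7% (nominal) |
| 0.8 / 0.6 | 0.87 | cheaper in 26.5% |
| 1.0 / 0.7 | 0.77 | cheaper in 51% |
| 1.0 / 0.5 | 0.69 | cheaper in 88% |
| 1.2 / 0.7 | 0.62 | cheaper in 89% |
| 0.5 / 1.0 | 1.45 | dearer in 89% |

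In the four rows where lesioning is the more skewed, a Welch comparison of means calls lesioning cheaper in about 3–7%. If the true lesioning mean is 10% higher in those rows, rank sum still says cheaper in 6%, 24%, 66% and 73%, against 0.4–2.5% for Welch.

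**Step 4: expensive minority instead of smooth skew.** Base and extra costs are log-normal with log-SD 0.4, so each mean is its median × exp(0.08) = median × 1.083.

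- *Tail in lesioning only.* The resection median is 100, so its mean is 108.3. The lesioning median is 75, with an extra cost of median 250 in 10%: 81.25 + 0.10 × 270.8 = 108.3. The means are equal, yet rank sum says cheaper in about 86% of trials, against about 5% for Welch.
- *Tail frequencies taken from the impairment rates, 2% and 11%.* The resection mean is 108.3 + 0.11 × 270.8 = 138.1. With the lesioning base set so that its mean is also 138.1, rank sum calls lesioning cheaper in 0% and dearer in about 46%.
- *Same rates with equal base costs.* Lesioning is truly cheaper: 108.3 + 0.02 × 270.8 = 113.7 against 138.1. Rank sum detects this in about 20% of trials and Welch in 52%.

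**Step 5: why the operation's cost needs to be defined.** Take follow-up costs of mean 0.8 (lesioning) and 1.0 (resection), log-SD 0.5. Rank sum on follow-up cost alone says cheaper in about 85% of trials. With operation costs of 3.5 and 3.0, total means are 4.3 and 4.0, so lesioning is 7.5% dearer. With 2.5 and 3.0 they are 3.3 and 4.0, so it is cheaper by more than follow-up alone suggests in absolute terms (0.7 against 0.2).

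**The case against.** **The rule is generic.** It does not mention costs, the article states no mean-cost estimand and promises no claim of cheapness, and a separate cost analysis may sit in an analysis plan that is not shown. That is fair and lowers the weight of the point. But the rule as published covers every continuous variable, cost is one of them, and following it gives no mean difference for skewed costs.

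**The rank sum test is not invalid.** It tests whether one arm tends to have lower costs than the other, and the percentages in the working are errors only if its result is read as a statement about mean cost. That is correct. It is also how a cost comparison is ordinarily read.

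**A reader might infer that the rule favours lesioning.** The documents do not support that direction. It needs lesioning to have the heavier tail. The article's own impairment rates, used as tail frequencies, give the opposite result, and equal shapes give no error.

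**A reader might also infer that the operation's cost is left out of the outcome.** No section says so. The cost is recorded, Table 1 has a follow-up at 7 ± 2 days at which the surgical admission could be counted, and costs at a visit could be cumulative from surgery. What stands is that inclusion is not stated.

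**Some costs may be unobserved under any test.** The withdrawal section ends follow-up when other epilepsy surgery is required, so later costs of those patients may be missing. Changing the test does not cure that.

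**Conclusion.** The concern holds in a limited form. The only stated rule for continuous data would usually send skewed costs to a rank sum test and medians, and neither estimates the difference in mean cost per patient. When the arms differ in skew, the result can mislead about mean cost in either direction: at 96 per arm and equal true means, lesioning is called cheaper in about 27–89% of trials or dearer in about 46–89%, depending on which arm has the heavier tail. When the shapes are the same, the rate is nominal.

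These sizes rest entirely on assumed distributions, and the direction cannot be predicted from the documents. Whether the operation's cost is counted is a definition to clarify, not a demonstrated omission. Cost is a secondary outcome with no stated decision attached, so the point is minor.

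**What to change.** - For medical costs, replace the normality-test rule by the difference in arithmetic mean cost per patient between lesioning and resection, with a bootstrap 95% confidence interval, or by a gamma model with log link. Report medians, quartiles and the rank sum test as supportive.
- Define the outcome as total epilepsy-related medical cost from the index operation, operation included, to 12 months. Keep visit-by-visit costs as description.
- State how costs are handled for patients whose follow-up ends before 12 months.

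This needs a few sentences in the analysis plan and one derived variable. The operation's cost is already to be recorded; because Table 1 has no cost row, the sponsor should confirm that the case report form captures the follow-up costs. The interval for a mean difference will usually be wider than the rank test suggests, which reflects how uncertain mean cost is.

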### Participant selection

The study is expected to enroll 240 participants. All participants will be recruited from the outpatient clinics of three centers and will be fully explained at the time of recruitment and will sign a written informed consent form. Minor participants and their legal guardians will also be fully explained about the study, and the written informed consent will be signed by their legal guardians.

Patients will be eligible for inclusion in the study only if all of the following criteria are applied:Age ≥ 3 years at enrollmentMeets the ILAE guidelines for the diagnosis of drug-resistant epilepsy with persistent disabling seizures (at least 1 or more per month); seizures persist after 2 years of standardized treatment with at least one or more first-line antiepileptic drugsWith a definite epileptogenic zone by preoperative comprehensive evaluation, which belonged to focal epilepsy, and are suitable for stereotactic RF-TC, stereotactic LITT, or resective surgeryAbility to understand and speak Mandarin Chinese

Patients with the following conditions will be excluded:

Epileptogenic foci cannot be accurately located or multiple epileptogenic foci are suspected after a comprehensive evaluation, which are not suitable for the operation included in this study.Pregnant or breastfeedingContraindications to surgeryHistory of previous operation for the purpose of treating epilepsyInclusion in any other clinical trialOther conditions that the researcher thinks he/she is not suitable to participate in the study

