### Randomization and blinding

Randomization will be performed by independent investigators with the SAS (9.3, SAS Institute Inc., Cary, NC, USA) software. The resulting list of random numbers has been placed into sequentially numbered, sealed, opaque envelopes. Based on the information obtained from the envelopes, consecutively enrolled participants will be randomly assigned, in a 1:1 ratio, to stereotactic lesioning or classical epileptogenic zone resective surgery. Patients who are assigned to stereotactic lesioning surgery will be also assigned in a 4:1 ratio to a subgroup of RF-TC and a subgroup of LITT. The same group of neurosurgeons at different centers (three groups in total) will be responsible for different procedures for each participant.

Researchers and clinical research coordinators participate in the grouping process. Clinical research coordinators are responsible for informing patients, but they are not involved in the patient assessment and treatment process. All subjects and clinicians will be aware of the trial group assignments before surgical treatment, outcome assessors. However, outcome assessors and statisticians will not be aware of the subgroups of subjects

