### Sample size

According to earlier studies and the previous work of our research team, the effective rates of stereotactic EEG-guided RF-TC, MRI-guided stereotactic LITT, and resective surgery are similar, and the rates of postoperative neurological impairment are 2%, 2%, and 11%. We expect to use a one-sided 95% confidence interval, a noninferiority limit of 10%, and an expected withdrawal rate of 20%. Therefore, we expect to enroll a total of 240 patients in this study. Patients will be recruited from outpatient and MDT with strict inclusion criteria.

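### Minor: read literally, the analysis rule compares ordered Engel class by an unordered chi-square test, and it names no exact method for the very sparse LITT impairment tables

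*Protocol article*

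**What the plan says.** Under Statistical analysis the protocol article assigns tests by type of variable. Normally distributed continuous variables get the t-test, other continuous variables get the rank-sum test, and for the rest: "The chi-square test will be used to compare the categorical data". The level is given as "Take the test level *α* = 0.05", without saying whether it is one- or two-sided. No ordinal test and no exact or small-count alternative is named.

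The list of secondary outcomes opens with "Engel classification at one-year follow-up after surgery". It does not say whether all classes are compared or only class I against the rest. The proportion with neurologic impairment is second on the list.

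On numbers, "The study is expected to enroll 240 participants". They are "randomly assigned, in a 1:1 ratio, to stereotactic lesioning or classical epileptogenic zone resective surgery", and the lesioning arm is then "assigned in a 4:1 ratio to a subgroup of RF-TC and a subgroup of LITT". The Sample size section adds "an expected withdrawal rate of 20" percent and impairment rates of 2% (RF-TC), 2% (LITT) and 11% (resection). The Abstract gives comparison of all three procedures as the aim.

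**The concern.** Engel class runs from best to worst. A chi-square test on a table of two arms by four classes has 3 degrees of freedom and spreads its sensitivity over every pattern of difference, including patterns with no direction. The article itself expects a direction: the Abstract says seizure freedom is less likely after the two lesioning procedures. If the whole distribution moves that way, an ordinal test detects it more often. This matters in a trial whose Sample size section assumes similar effective rates, because a missed shift on the standard seizure-outcome scale could be read as similarity.

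The second strand is sparse data. The rule covers every categorical comparison, including any made with a LITT subgroup of about 24 patients in whom less than one impairment event is expected.

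**Working it through.** **Inputs from the article.** 240 enrolled at 1:1 gives 120 per arm; 20% withdrawal leaves 120 × 0.8 = 96. The 4:1 split gives 96 RF-TC and 24 LITT, or about 77 and 19 after withdrawal. Impairment rates are 2%, 2% and 11%. The Background gives a seizure-free range of 50–80% after surgery.

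**Assumed, because the article is silent.** The Engel class distribution, the size and shape of any difference, and a two-sided 5% level. (The Sample size section says "We expect to use a one-sided 95% confidence interval", but that concerns non-inferiority.) The plan has no power figure for Engel class to reproduce.

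**1. Uniform shift.** For each cut-point j, odds(class ≤ j) under lesioning = OR × odds(class ≤ j) under resection. Example: class I 65% has odds 0.65/0.35 = 1.857; with OR 0.50 the odds are 0.929, so class I is 48.1%. Simulated power at 96 per arm:

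| Resection I/II/III/IV (%) | OR | Chi-square, 3 df | Wilcoxon | Class I yes/no |
|---|---|---|---|---|
| 65/15/10/10 | 0.60 | 29% | 43% | 40% |
| 65/15/10/10 | 0.50 | 52% | 70% | 65% |
| 65/15/10/10 | 0.45 | 66% | 82% | 78% |
| 65/15/10/10 | 0.40 | 80% | 91% | 88% |
| 65/15/10/10 | 0.30 | 97% | 99% | 99% |
| 50/20/15/15 | 0.50 | 58% | 75% | 65% |
| 50/20/15/15 | 0.40 | 84% | 94% | 87% |
| 80/10/5/5 | 0.45 | 52% | 70% | 69% |
| 80/10/5/5 | 0.40 | 66% | 82% | 81% |

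For OR 0.40–0.60 the rank test gains about 9 to 18 points in the cases run. Allowing for simulation error and other splits of classes II–IV, take 9 to 19. At OR 0.30 the gain is about 2 points in the 65% case. Theory agrees: a directional signal with 80% power on 1 df has 64.5% on 3 df. The class I dichotomy loses about 0 to 10 points against the rank test.

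**2. Non-uniform difference.** Take 65/15/10/10 v 45/35/10/10, where 20% of patients move from class I to II and nobody moves further. Chi-square has 82% power and the rank test about 57%. The class I proportion alone does well here. The standard error is √(2 × 0.55 × 0.45/96) = 0.072, so z = 0.20/0.072 = 2.79. Power is about Φ(2.79 − 1.96) = Φ(0.83), or roughly 80%.

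**3. Sparse tables, impairment.**

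- LITT v RF-TC: expected LITT events are 24 × 0.02 = 0.48 (19 × 0.02 = 0.38). With one LITT event and none in RF-TC, Pearson chi-square = N·n₂/[n₁(N − 1)] = 120 × 96/(24 × 119) = 4.03, above the critical 3.84. With 19 v 77 it is 96 × 77/(19 × 95) = 4.10. So one event counts as significant, although the chance that a single event falls in LITT is 24/120 = 20%. At a true 2% in both groups, that table alone has probability 0.48 × 0.98¹¹⁹ = 4.3%. Enumerating all tables gives a true size of 8.2% (24 v 96) and 8.7–8.9% (19 after withdrawal).
- LITT v resection: the expected LITT count under the pooled rate is 24/144 × (0.48 + 13.2) = 2.28, or 19/115 × (0.38 + 10.56) = 1.81. Both are below 5, yet the exact size is only 3.7–6.4% for common rates of 2–11%.
- Main 1:1 comparison: (96 × 0.02 + 96 × 0.11)/2 = (1.92 + 10.56)/2 = 6.2 expected events per arm.

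**4. Sparse tables, Engel.** With 19–24 LITT patients, expected counts in classes II–IV are about 1 to 5, but the simulated size of the chi-square is 4.5–5.1%.

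**The case against.** The strongest reply is that the article never ties Engel class to a four-class chi-square. The sentence is generic, and the article often speaks in binary terms: its regression analysis concerns factors associated with seizure freedom. If Engel class I is compared yes/no, a 2×2 chi-square is directional and little is lost. This is also a condensed article, and the coding of a secondary scale or a fallback for small cells is commonly left to an analysis plan. Most of this stands, and it is why the point is minor. It does not remove the point. The outcome is listed as a classification, nothing dichotomises it for the comparison of arms, and the stated rule places the rank test elsewhere. An analysis plan that used an ordinal method would depart from the published rule.

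A reader might infer that the plan loses about 15 points of power. The article does not support a fixed figure, because distribution, effect and power are all absent and the sign depends on the shape of the difference. A non-uniform pattern is plausible here: the Abstract's lower seizure freedom and the Sample size section's similar effective rates could both hold if patients move from class I to a neighbouring class.

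A reader might also infer that chi-square results are unreliable for all LITT comparisons and for impairment generally. The calculated sizes do not bear that out beyond LITT v RF-TC impairment. Nor does naming a test prevent proportions and differences from being reported.

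**Conclusion.** The point holds as a minor one about secondary outcomes. The stated rule, taken literally, ignores the order of the Engel scale. The cost is roughly 9–19 points of power under an assumed uniform shift (class I 50–80%, OR 0.40–0.60, 96 per arm, two-sided 5%). It is only a few points when power is already high, and negative for an adjacent-class difference such as 82% v 57%. If the intended analysis is class I yes/no, about 0–10 points are at stake.

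The sparse-data strand is narrower. The Pearson test is clearly anti-conservative for LITT v RF-TC impairment at 2% (true size about 8–9%). It is close to nominal for LITT v resection impairment and for Engel tables with LITT, and the main 1:1 impairment comparison raises no such difficulty. Nothing here touches the primary outcome or the figure of 240.

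**What to change.** In Statistical analysis, add that Engel class I–IV is compared between the two randomised arms by the Wilcoxon rank-sum test or a proportional-odds model, reporting a common odds ratio with its confidence interval. Add the difference in the class I proportion with its interval. For impairment comparisons involving LITT, specify an exact test, or a score or exact interval; the main 1:1 comparison can keep the chi-square test.

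The cost is a sentence or two, settled before unblinded analysis, with no new data. There is a small statistical price. The ordinal test is less sensitive to non-uniform differences, which the class I proportion partly covers. The common odds ratio needs the proportional-odds assumption as a summary, while the rank test does not. Exact tests are conservative at such low counts.

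### Noninferiority is planned with intention-to-treat as the only named analysis; switching between operations would shrink a true deficit, so a per-protocol analysis should have to agree

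*Protocol article*

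**What the plan says.** All of this is in the protocol article; no separate analysis plan is shown.

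- **Analysis set.** Statistical analysis: "Analysis of the primary outcome will be by intention-to-treat". No other set is named for this outcome. The same section sets the level with "Take the test level *α* = 0.05", without saying one- or two-sided.
- **Noninferiority.** Sample size: "We expect to use a one-sided 95% confidence interval, a noninferiority limit of 10%, and an expected withdrawal rate of 20"%. The endpoint to which the limit applies is not named. The section says that "the effective rates of stereotactic EEG-guided RF-TC, MRI-guided stereotactic LITT, and resective surgery are similar", giving no figure, and that "the rates of postoperative neurological impairment are 2%, 2%, and 11"%. Neurological impairment is a secondary outcome.
- **Allocation and its disclosure.** Patients are allocated "in a 1:1 ratio, to stereotactic lesioning or classical epileptogenic zone resective surgery". The Randomization and blinding section adds: "All subjects and clinicians will be aware of the trial group assignments before surgical treatment". Table 1 heads the allocation column at day −7 and the operation column at day 0.
- **End of follow-up.** The section on withdrawal ends follow-up when other epilepsy surgery is needed. The Interventions section ties a change of medication or a further procedure to an exacerbation and leaving the study.

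**The concern.** In a superiority trial, departures from the allocated treatment usually make intention-to-treat cautious. In a noninferiority trial, some departures have the opposite effect. If patients allocated to lesioning are resected, or the reverse, the arms become more alike and a real deficit is harder to see. Similar shares of untreated patients in both arms do the same.

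This trial is open to that. Treatment is not masked before surgery, the operations differ greatly in invasiveness, and there is about a week in which to decline or change. The Abstract itself expects seizure freedom to be less likely with lesioning, so a true deficit is realistic. At stake is a claim that lesioning is no worse than an established operation, made partly because some lesioning patients were resected.

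**Working it through.** **The plan's own figure.** The article gives: "Therefore, we expect to enroll a total of 240 patients in this study". It states neither power nor an effective rate, so 240 cannot be reproduced. For equal rates p, the size per arm is 2p(1−p)(1.645 + 0.842)²/0.10². At p = 70% and 80% power this is 260 per arm, 520 in total, and 520/0.8 = 650 with 20% withdrawal. The figure 240 (96 evaluable per arm) fits 80% power only if p is about 91.6%. This does not show 240 to be wrong, and the present point does not depend on it.

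**Inputs.** From the article: 240 patients allocated 1:1, so 120 per arm; limit 0.10; one-sided 5%, so z = 1.645. Assumed: success of 70% after resection and 60% after lesioning, which is a true deficit exactly at the limit; 10% success without an operation; switchers do as well as others who have the operation they received; all outcomes observed. The article gives no success proportions and no switching rate.

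**Formula.** With d = p(resection) − p(lesioning) as seen under intention-to-treat, and SE = √[p_R(1−p_R)/120 + p_L(1−p_L)/120],

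P(noninferiority concluded) = Φ((0.10 − d)/SE − 1.645).

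If a share f of the lesioning arm is resected, p_L = 0.60 + 0.10f. If the same share of the resection arm also switches, p_R = 0.70 − 0.10f. If a share f of an arm is untreated, its rate becomes (1−f)p + 0.10f.

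| Departure | p_R v p_L | d | SE | Wrongly noninferior |
|---|---|---|---|---|
| none | 70% v 60% | 0.10 | 0.0612 | 5.0% |
| 10% of lesioning arm resected | 70% v 61% | 0.09 | 0.0611 | 6.9% |
| 20% of lesioning arm resected | 70% v 62% | 0.08 | 0.0609 | 9.4% |
| 10% switch in each arm | 69% v 61% | 0.08 | 0.0614 | 9.4% |
| 20% switch in each arm | 68% v 62% | 0.06 | 0.0614 | 16.0% |
| 20% untreated in each arm | 58% v 50% | 0.08 | 0.0641 | 9.1% |
| 20% untreated, lesioning arm only | 70% v 50% | 0.20 | 0.0619 | 0.06% |
| 20% untreated lesioning, 10% resection | 64% v 50% | 0.14 | 0.0633 | 1.1% |

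**Range.** With resection success of 60% to 90% and lesioning always 10 points lower, 20% one-way switching gives 9.1% to 11.6%, and 20% two-way switching gives 15.4% to 21.9%.

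**What a careless per-protocol set would do.** Suppose 10% of the lesioning arm (12 of 120) are failures who are re-operated and dropped. Then 72 successes among 108 give 66.7% v 70%, so d = 0.033, SE = √(0.21/120 + 0.222/108) = 0.0617, and this analysis alone passes wrongly 28.6% of the time.

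**Power.** With equal true rates, power is Φ(0.10/√[2p(1−p)/n] − 1.645). At p = 70%: n = 120 gives Φ(1.690 − 1.645) = 52%, and n = 96 (all 20% lost) gives Φ(1.512 − 1.645) = 45%.

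**The case against.** The strongest reply is that the article is a condensed text. Naming intention-to-treat is not an error and does not exclude a per-protocol analysis; one may be in the full protocol or the analysis plan. That stands. A reader might infer that the trial has ruled out a second set, and the article does not say so. What remains is that the article does fix the analysis of the primary outcome, and the set or sets on which noninferiority may be claimed belong to that decision.

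Four further limits also stand.

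- A reader might infer that every patient who misses the allocated operation favours noninferiority. The last two rows of the table show otherwise.
- A reader might take the 20% as the diluting share. It is expected withdrawal, not switching, and its direction depends on how missing outcomes are handled. No switching rate is given.
- The limit is not expressly tied to the primary outcome, and that outcome is a percentage reduction in seizure frequency without a responder threshold. Efficacy is the natural reading, because impairment is expected to be lower with lesioning (2% v 11%), but it remains a reading.
- Per-protocol is not automatically stricter: dropping re-operated patients can flatter the arm with more failures.

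**Conclusion.** The point holds in a limited form. The article plans noninferiority, names only intention-to-treat for the primary outcome, and lets patients and clinicians know the arm before surgery. If patients switch operations, or similar shares in both arms go untreated, intention-to-treat understates a true deficit. For shares of 10-20%, the nominal 5% error becomes 6.9-9.4% with one-way switching and 9.4-16.0% with two-way switching. These figures rest on an assumed binary success of 70% v 60%, complete outcomes, and switching that is unrelated to prognosis.

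The documents do not support the stronger reading that intention-to-treat is lenient here whatever happens, or that the expected withdrawal by itself inflates the error. Confidence is medium because the fuller documents are not shown. The change is worth making: requiring a second analysis to agree cannot raise the chance of a false noninferiority claim above that of intention-to-treat alone.

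**What to change.** 1. State that the 10% limit applies to the efficacy endpoint, and define that endpoint on a scale where a 10% limit has meaning.
2. Keep intention-to-treat. Add a per-protocol analysis of patients who received the allocated operation, with the same one-sided 95% interval and the same limit. Claim noninferiority only if both analyses meet the limit.
3. In both analyses, count patients who need other epilepsy surgery, or who withdraw after an exacerbation, as failures; do not drop them. If percentage reduction is kept as the scale, say what value a failure receives.
4. State how other withdrawals are handled, since that decides the direction in which the expected 20% acts.

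The cost is a few sentences and one more table from data already collected. Power falls somewhat: at an assumed 70% effective rate, from 52% to 45% if the per-protocol set loses all 20%. The per-protocol set is not protected by randomisation, so it should stand beside intention-to-treat and not replace it.
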